## **5.2. Exclusion criteria**

1. Baseline erythrodermic or pustular psoriasis or any other skin diseases (e.g. eczema) that can affect and/or complicate the assessment of psoriasis treatment with the study drugs.
2. The patient had been exposed to any monoclonal antibodies inhibiting TNF $\alpha$ .
3. The patient had used two or more monoclonal antibodies (or their fragments) against other targets.
4. Less than 12 weeks have passed between the patient stopped using the monoclonal antibody therapy and signing the informed consent form for this study.
5. The patient had used or now uses any of the following concomitant therapies:
  - Systemic (oral or parenteral) glucocorticoids or systemic retinoids (acitretin) within 4 weeks before the date of signing the informed consent form or during the screening period.
  - Systemic non-biologic medications including (but not limited to) methotrexate, sulphasalazine, cyclosporine, mycophenolate mofetil, apremilast, etc. within 4 weeks before signing the informed consent form; OR leflunomide or cyclosporine within 6 months before signing the informed consent form.
  - Phototherapy [including selective phototherapy (UVB) and photochemotherapy (PUVA)] within 4 weeks before signing the informed consent form.
6. Vaccination with live or attenuated vaccines any time within 8 weeks before signing the informed consent form.

7. The patient had a major surgery within 30 days before signing the informed consent form or a major surgery is planned during the study.
8. The patient has an active infection at screening or has a history of any infections meeting the criteria below:
  - Any active infection that required systemic anti-infectious agents within 28 days before signing the informed consent form.
  - Any infection that required hospitalization or intravenous and/or intramuscular administration of anti-infectious agents within 8 weeks before signing the informed consent form.
  - Recurring, chronic or any other active infection if the investigator believes that the study drug can harm the patient.
9. Documented HIV-infection or a history of a severe immunodeficiency of any origin.
10. HBs antigen, antibodies to HBcor antigen and/or antibodies to hepatitis C virus revealed at screening.
11. Ongoing tuberculosis or a history of tuberculosis.
12. A positive microprecipitation reaction (MPR) together with a positive *T. pallidum* hemagglutination assay (TPHA) at screening. If results of any of the two assays are positive, the patient has to undergo additional examinations. In the case of a positive *T. pallidum* hemagglutination test and negative microprecipitation test, additional examinations include as follows:
  - If the patient has a history of syphilis, appropriate medical records should be provided confirming the adequate therapy for syphilis.
  - ELISA [ELISAtotal or ELISA(IgG)+ELISA(IgM)], or immunofluorescence reaction with absorption, or *T. pallidum* immobilization test.
  - The dermatology/venereology specialist confirms that the patient has or has no syphilis.

---

 A surgery associated with a high risk of severe blood loss (> 10% of the circulating blood volume) or any other life-threatening event.

 The screening examination includes tests for HBsAg and total antibodies to HBcor antigen (IgG+IgM). If the patient tested negative for these markers (HBsAg and anti-HBcor total), he/she is considered eligible for the study with respect to this criterion. If the patient tested positive for HBsAg, the patient cannot be included in the study regardless of the results for anti-HBcor. If the patient tested negative for HBsAg but positive for anti-HBcor-total, the patient has to undergo additional examinations. Additional examinations include but were not limited to the following: qualitative PCR for HBV DNA, anti-HBcor-IgG, anti-HBcor-IgM, blood biochemistry, and a consultation with an infectious disease specialist. Having considered the examinations and test results, the Sponsor decides whether to approve such a patient for the study.

 The screening examination includes a test for anti-HCV antibodies in the blood. If the patient tests negative for anti-HCV, he/she is considered eligible for the study with respect to this criterion. If the patient tests positive for anti-HCV, the patient has to undergo additional examinations. Additional examinations include but were not limited to the following: qualitative PCR for HCV RNA, blood biochemistry, and consultation with an infectious disease specialist. Having considered the examinations and test results, the Sponsor decides whether to approve such a patient for the study.

 If hemagglutination test cannot be performed, ELISA total or ELISA(IgG)+ELISA(IgM) should be done instead. In the case of positive results, the algorithm is the same as after a positive hemagglutination assay.

- If the *T. pallidum* hemagglutination test is negative and the microprecipitation test is positive, further examinations include as follows:
- Repeated microprecipitation (or VDRL) and a specific assay should be performed: immunofluorescence assay or ELISA (ELISAtotal or ELISA(IgG)+ELISA (IgM)).
- The dermatology/venereology specialist confirms that the patient has or has no syphilis.
- Having considered the report from the dermatology/venereology specialist and the results of additional examinations, the Sponsor decides whether to include this patient in the study.

13. Baseline concomitant medical conditions that can increase the risk of adverse events during the study therapy, affect the assessment of the severity of psoriasis, mask, aggravate, or alter the symptoms of psoriasis, or result in the same clinical and/or laboratory and/or instrumental symptoms as those of psoriasis:

- Acute inflammatory diseases or relapses of chronic inflammatory diseases other than psoriasis.
- Stable angina class III-IV, unstable angina or a history of myocardial infarction within 1 year before signing the informed consent.
- Moderate to severe cardiac failure (NYHA classes III and IV).
- Severe treatment-resistant hypertension;
- Atopic asthma and/or a history of angioedema.
- Moderate to severe respiratory failure and/or COPD grade 3/4.
- Decompensated diabetes mellitus.
- Systemic autoimmune diseases (including systemic lupus erythematosus, Crohn's disease, ulcerative colitis, systemic scleroderma, inflammatory myopathy, mixed forms of inflammatory diseases of the connective tissue, overlap syndrome, etc.).
- Active neurological diseases, such as multiple sclerosis, Guillain-Barre syndrome, optic nerve neuritis, transverse myelitis, or a history of neurological symptoms suggesting demyelinating diseases of the central nervous system.
- Any other concurrent diseases (including but not limited to metabolism, blood, kidney, liver, lung, neurological, endocrine, heart, and GI disorders and/or infections) that, in the investigator's opinion, may affect the course of psoriasis, confound the assessment of its symptoms, or put the study subject at unacceptable risk during the treatment with BCD-057/Humira®.

---

 Resistant hypertension includes all cases of hypertension that are not controlled by the concurrent use of three anti-hypertensive drugs of different classes, including a diuretic, and non-medication methods (salt-free diet, controlled physical exercise).

14. Malignancies in remission for less than 5 years, except for adequately treated (cured) squamous and basal cell carcinoma, cervical cancer *in situ* or ductal breast carcinoma *in situ*.
15. A history of hypersensitivity to adalimumab or any excipients of Humira® and/or BCD-057 (mannitol, citric acid monohydrate, sodium citrate, sodium hydrogen phosphate dihydrate, sodium dihydrogen phosphate dihydrate, sodium chloride, polysorbate 80, sodium hydroxide).
16. Known allergy to monoclonal antibodies (murine, chimeric, humanized or fully human).
17. Pregnancy, breastfeeding or planning for pregnancy while participating in the study.
18. Any psychiatric disorders, including a history of major depression and/or suicidal thoughts that can, in the investigator's opinion, put the patient at risk or affect patient's ability to follow the study protocol.
19. Use of recreational drugs, alcohol and/or medications and/or psychoactive substance abuse problems.
20. Participation in any other clinical study within 3 months before screening or simultaneous participation in other clinical studies.
21. Patients who were randomized to this study and then discontinued the study due to any reasons (i.e. patients who met all other inclusion/exclusion criteria), cannot be re-enrolled in this study.

### 5.3. *Withdrawal criteria*

The patient will be withdrawn from the study in the following circumstances:

1. Major violations of inclusion and/or exclusion criteria revealed after the enrollment (patients removed at the discretion of JSC BIOCAD).
2. The patient recalls his/her consent to participate in the study.
3. The patient develops adverse events or serious adverse events, laboratory abnormalities or comorbidities that, in the investigator's opinion, make further participation in the study impossible, dangerous or non-beneficial regarding patient's well-being and/or safety.
4. The patient misses more than 4 injections and/or visits during the study (compliance < 85%) or misses 2 consecutive injections and/or visits, or breaches the specified time windows for more than 5 visits.
5. The patient develops active tuberculosis. If the patient has indeterminant or positive results of the QuantiFERON assay or T-Spot.TB or Diasptest® at Week 25, he/she can continue the study only if all three of the following requirements are met:

---

 Patients whose screening was interrupted due to force majeure circumstances (external events beyond the patient's and investigator's control) could be re-screened in this study.

 Deviations from inclusion and/or exclusion criteria justified by the investigator and approved by the Sponsor are not considered a reason for withdrawal.

- The patient tests negative in one additional QuantiFERON / T-Spot.TB assay.
  - The chest X-ray shows no signs of active tuberculosis.
  - The TB specialist confirms that the patient has no tuberculosis.
  - Otherwise, the patient has to be removed from the study.
6. The patient gets pregnant. If pregnancy is suspected, the urine test for HCG must be performed. If the test gives a positive result, the patient must be withdrawn from the study (follow-up procedures are described in section 5.4).
  7. The patient has a major depressive disorder or suicidal ideation or makes suicidal attempts.
  8. The study is terminated by the decision of JSC BIOCAD, local ethics committees or regulatory authorities.
  9. The patient used medications prohibited by the Protocol.
  10. The patient dies.

***The investigator must inform JSC BIOCAD within 24 h about a patient's premature withdrawal and specify the reason.***

#### ***5.4. Follow-up of subjects withdrawn from the study or subjects who discontinued the study treatment but remain in the study for follow-up***

##### ***5.4.1. Follow-up of patients who received at least one dose of BCD-057/Humira®***

The following should be done if the patient who received at least one injection of BCD-057/Humira® discontinues the study early:

- At the withdrawal day, the investigator should perform the Early Termination Visit and fill out the source documents together with the Unscheduled Visit section of the CRF. On this visit, the following procedures should be performed: collecting data on concomitant therapy, physical examination, and measuring blood pressure and body temperature.

The Early Withdrawal visits are mandatory for all subjects who prematurely withdraw from the study, except for the subjects who are lost to follow-up or are physically unable to attend the visit. All records must be supported with appropriate source documents.

If the subject discontinues the study due to an AE/SAE, the investigator should conduct further treatment and follow-up after the Early Withdrawal Visit in accordance with the study site standards for the treatment of a certain AE/SAE. The patient should be followed up until **the AE or SAE resolves completely**. In addition, an Additional Early Termination Visit is performed 28±2 days later (procedures are described above).

The female patient withdrawn from the study due to pregnancy that occurred during the study period should be followed up through the entire pregnancy and for 6 months after delivery to evaluate the mother's and child's health. These follow-up procedures can be performed only if the woman has given her consent. Information on pregnancy course and outcome should be recorded in the source documentation. During the entire period of pregnancy, the investigator in collaboration with the attending Ob/Gyn specialist should monitor the patient's overall health, the course of pregnancy, and laboratory values including ultrasound. When the child is born, the investigator together with the attending pediatrician should monitor the newborn for 6 months evaluating the child's clinical status and the laboratory/instrumental findings.

Information regarding the health state of all dropouts should be recorded in their source documentation and CRFs.

***5.4.2. Follow-up of patients who did not receive a single dose of BCD-057/Humira®***

If the subject discontinues the study before dosing, the Early Withdrawal Form (eCRF) should be filled out on the day of withdrawal. Non-dosed patients are followed-up only if they discontinue the study because of AEs/SAEs. In this case, the follow up is performed according to the study site standards.

If the subject is withdrawn from the study due to any reason after receiving at least one dose of BCD-057/Humira®, his/her data will be included in the analysis. If the subject is withdrawn from the study before dosing, his/her information will be removed from the analysis.

## **6. Treatment of study subjects**

### **6.1. Study therapy**

#### **6.1.1. Treatment regimen and duration**

Patients in both arms will receive adalimumab as a SC injections according to the following scheme: 80 mg on Day 1 of Week 0 followed by 40 mg on Day 1 of Week 1, Week 3, Week 5, Week 7, Week 9, Week 11, Week 13, Week 15, Week 17, Week 19, Week 21, Week 23, Week 25, Week 27, Week 29, Week 31, Week 33, Week 35, Week 37, Week 39, Week 41, Week 43, Week 45, Week 47, Week 49, and Week 51.

The patients will be followed up until Week 55.

##### **6.1.1.1. Use of the test drug and reference drug**

The patients who met the eligibility criteria will be centrally randomized (with double blinding) into one of the study arms at a 1:1 ratio.

- Patients allocated to Arm 1 (n = 172) will receive BCD-057 (JSC BIOCAD) at a dose of 80 mg on Day 1 of Week 0 followed by a dose of 40 mg on Day 1 of weeks 1, 3, 5, 7, 9, 11, 13, 15, 17, 19, 21, and 23.
- Patients allocated to Arm 2 (n = 172) will receive Humira® at a dose of 80 mg on Day 1 of Week 0 followed by a dose of 40 mg on Day 1 of weeks 1, 3, 5, 7, 9, 11, 13, 15, 17, 19, 21, and 23.

To evaluate the effects of switching from the originator to the biosimilar, patients will be re-randomized at Week 24. As a result of this second randomization, patients from the Humira® arm will be assigned at a 1:1 frequency to one of the two sub-arms.

- Patients in sub-Arm 1 will stay on Humira® 40 mg and receive injections on Day 1 of weeks 25, 27, 29, 31, 33, 35, 37, 39, 41, 43, 45, 47, 49, and 51.
- Patients in sub-Arm 2 will receive injections of BCD-057 40 mg on Day 1 of weeks 25, 27, 29, 31, 33, 35, 37, 39, 41, 43, 45, 47, 49, and 51.

To maintain the double-blind study design, patients from the BCD-057 arm will also be invited for re-randomization. However, in this case, this will be just a nominal procedure where patients will be assigned new randomization IDs and lot numbers. They will continue BCD-057 according to the following regimen: 40 mg on Day 1 of weeks 25, 27, 29, 31, 33, 35, 37, 39, 41, 43, 45, 47, 49, and 51.

Regardless of the treatment arm to which they are assigned, patients will be followed up until Week 55 (if the patient has not been earlier removed from the study).

Patients who drop out due to reasons other than AEs/SAEs (not safety-related) can be replaced before Week 16 at the discretion of the Sponsor.

Injections of BCD-057/Humira® will be given at the study sites by a responsible qualified member of the study team (nurse, doctor, etc.).

#### ***6.1.1.1.1. Packaging and labeling of the investigational products***

In this study, each patient will use two individual study kits for the whole therapy cycle.

Each study kit contains 14 syringes (one kit for each study period) and has its own unique lot number labeled on the primary and secondary packaging.

All syringes will be packed in blisters. The study drug and the reference drug will have the same primary and secondary packaging. They will be identified only by the lot number. The syringes will not differ by color.

#### ***6.1.2. Preparation of the investigational products for administration, and administration procedure***

##### ***6.1.2.1. Test drug and reference drug***

Injections of BCD-057/Humira® will be given at the study sites by a responsible qualified member of the study team (nurse, doctor, etc.).

- Take the syringe from its packaging. Do not shake the syringe.
- Choose an injection site. It can be the abdomen or the anterior aspects of the thigh. Rotate injection sites to different areas for subsequent injections. Do not inject the drug into areas where the skin is swollen, hard or painful.
- Disinfect the skin at the planned injection site.
- Hold carefully the skin at the injection site and slightly pull it up.
- Remove the cap from the needle. With one quick, short motion, push the needle into the skin at a 90° angle.
- Inject the drug slowly by pushing the plunger for 2 to 5 seconds until the syringe is empty.
- Remove the needle from the skin.
- Press a cotton ball at the injection site.
- Do not massage or rub the injection site.
- There may be a small amount of blood at the injection site.

### ***6.1.3. Adjustment and discontinuation of study therapy***

#### ***6.1.3.1. Dose modification and discontinuation for the test or reference drug***

No dose modifications are allowed either for BCD-057 or Humira®. The patients should not compensate for missed doses of BCD-057/Humira® (e.g. the patient should not double the next dose of BCD-057/Humira® if he/she have missed the previous one).

During the treatment with adalimumab, the following events have been reported: infections (including tuberculosis and reactivation of hepatitis B), neurological disorders in patients with demyelinating diseases of the CNS, malignancies, allergies, hematological complications (including pancytopenia and aplastic anemia), lupus-like syndrome, and allergic reactions. Adalimumab should be discontinued if the patient develops a serious infection or sepsis, tuberculosis, a severe fungal infection, symptoms suggesting a demyelinating disease, a malignancy, serious allergic reactions, significant blood abnormalities, severe CHF and/or symptoms of lupus-like syndrome.

The investigator decides whether to discontinue the therapy (temporarily or permanently) taking into account the patient's complaints and general health state, physical exam results, laboratory values, and other factors indicating that continuation of the study therapy is not possible, dangerous to the patient or does not benefit the patient's well-being and safety.

#### ***6.1.3.2. Acceptable changes in visit schedule***

##### ***All patients***

In the case of adverse events - for not more than 14 days. If the AE does not resolve in 14 days and, in the investigator's opinion, poses the risk to patient's health, the patient has to be withdrawn from the study. However, if the investigator and the CRA believe that the patient who discontinued adalimumab for more than 14 days may get benefit from the therapy, **adalimumab treatment can be continued.**

##### ***Patients not involved in the PK study***

Due to any reasons not related to treatment - for not more than 7 days (this window can be extended if justified by the investigator and approved by the Sponsor).

##### ***Patients involved in the PK study***

Any deviations from the visit schedule are strongly discouraged. If necessary, the visit can be postponed for 3 days within the following periods: From Visit 1 (Week 0) to Visit 8 (Week 13) and from Visit 11 (Week 17) to Visit 14 (Week 23).

**Deviations from the visit schedule starting from Visit 9 (Week 15) and to Visit 10-3 (Day 6 of Week 16) are allowed only due to AEs/SAEs.**

Starting from Visit 15 (Week 24), visits can be postponed for not more than 7 days due to any reasons not related to therapy. This period can be extended if the investigator provides an appropriate justification and the Sponsor approved re-scheduling.

If the second or subsequent doses of BCD-057 are postponed, the dates of the next visits will be postponed to account for the actual date of the postponed dose, according to the study schedule. If the Protocol stipulates no injection on the postponed visit, the subsequent visits are performed according to the original schedule.

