| BP                    | Blood pressure                                                                                                                                                    |
| BSA                   | Body surface area affected by psoriasis                                                                                                                           |
| Cl                    | Total clearance                                                                                                                                                   |
| C max,ss   | Maximum concentration at steady state                                                                                                                             |
| C min      | Minimum concentration at steady state in any tau interval                                                                                                         |
| CNS                   | Central nervous system                                                                                                                                            |
| CRF                   | Case Report Form                                                                                                                                                  |
| CTCAE                 | Common Toxicity Criteria for Adverse Events                                                                                                                       |
| C trough   | Measured concentration at the end of a dosing interval at steady state (taken directly before next administration)                                                |
| DLQI                  | Dermatology Life Quality Index                                                                                                                                    |
| ECG                   | Electrocardiography                                                                                                                                               |
| ELISA                 | Enzyme-Linked Immunosorbent Assay                                                                                                                                 |
| EMA                   | European Medicines Agency                                                                                                                                         |

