| Study Therapy | 
Adalimumab will be injected to patients of both arms: 80 mg SC at Week 0 followed by 40 mg SC once every two weeks, starting from Week 1. The efficacy of this dosing regimen was established in large pivotal studies, the results of which supported the approval of adalimumab for the treatment of plaque psoriasis. This regimen is presented in the approved Russian Instruction for Medical Use (IMU) for Humira® (JIC-002422).
 
Injections of BCD-057/Humira® will be given at the study sites by a responsible qualified member of the study team (nurse, doctor, etc.). Throughout the entire study, the patients are not allowed to use phototherapy [including selective phototherapy (UVB) and photochemotherapy (PUVA)], systemic non-biological anti-inflammatory agents (methotrexate, sulfasalazine, chlorambucil, leflunomide, cyclosporine A, azathioprine, cyclophosphamide, cyclosporine, apremilast, mycophenolate mofetil, etc.), aromatic retinoids (acitretin), systemic glucocorticoids for the treatment of psoriasis (oral or parenteral), genetically engineered biological medicinal products, and live or attenuated vaccines.
 
Patients can use topical moisturizers, emollients, oils, salicylic acid products, topical antibacterial and antimycotic agents, and topical glucocorticoids as needed. All patients must discontinue all topical
 |

 Patients whose screening was interrupted due to force majeure circumstances (external events beyond the patient's and investigator's control) could be re-screened in this study.

 The Protocol allows single doses of systemic glucocorticoids to manage acute anaphylactic reactions, shock, or other life-threatening events that developed as adverse events in patients during the study.

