This study is to compare the pharmacokinetics of BCD-057 and Humira® in a limited patient population (90 subjects from each study arm, 180 subjects total). This investigation is necessary to demonstrate that pharmacokinetics of these drugs is similar not only in healthy volunteers but in psoriasis patients as well (who may differ from healthy subjects in terms of adalimumab PK). In patients with plaque psoriasis, adalimumab is used for a long time, so it is important to study its PK parameters at steady state – when an equilibrium between the intake of the drug and its elimination has been achieved. Adalimumab fully exerts its clinical effects when reaches the steady state concentration. In addition, steady-state PK allows predicting how rapidly the serum levels of the active ingredient decrease is the patient misses a dose or discontinues the drug.

It is known that the time to steady state equals 3 to 5 half-life periods of adalimumab. For adalimumab, the average half-life is 2 weeks, varying from 10 to 20 days [8]. Thus, the maximum time to steady state will be 100 days or 14.3 weeks ( $20 \times 5 = 100$ ). According to literature data, adalimumab concentrations reach the steady state in 12 to 16 weeks. Blood specimens will be

---

 Adalimumab M04-688 Pharmacokinetic Report

[http://www.abbvie.com/assets/research/clinical-trials-data-and-information-sharing/synopses/adalimumab\\_M04-688.pdf](http://www.abbvie.com/assets/research/clinical-trials-data-and-information-sharing/synopses/adalimumab_M04-688.pdf)

taken at frequent intervals after the 9th injection of adalimumab (at weeks 15 and 16), and thus the PK of BCD-057/Humira® will be studied at steady state.

In the second period of the study, some patients will be crossed over from one drug product to another. After completing Week 24 and all appropriate assessments, one half of patients from the Humira® arm will be switched to BCD-057. The rest of patients who were originally randomized to receive Humira® will continue the treatment with Humira®.

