|                           |                                                                                      | Day 2 of Week 15, 24 h $\pm$ 30 min after the 9 th injection of adalimumab (PK11),
Day 3 of Week 15, 48 h $\pm$ 90 min after the 9 th injection of adalimumab (PK12),
Day 4 of Week 15, 72 h $\pm$ 120 min after the 9 th injection of adalimumab (PK13),
Day 5 of Week 15, 96 h $\pm$ 120 min after the 9 th injection of adalimumab (PK14),
Day 6 of Week 15, 120 h $\pm$ 120 min after the 9 th injection of adalimumab (PK15),
Day 7 of Week 15, 144 h $\pm$ 120 min after the 9 th injection of adalimumab (PK16),
Day 2 of Week 16, 192 h $\pm$ 120 min after the 9 th injection of adalimumab (PK17),
Day 4 of Week 16, 240 h $\pm$ 120 min after the 9 th injection of adalimumab (PK18),
Day 6 of Week 16, 288 h $\pm$ 120 min after the 9 th injection of adalimumab (PK19),
Day 1 of Week 17, 15 min before the injection of adalimumab (PK20),
Day 1 of Week 19, 15 min before the injection of adalimumab (PK21),
Day 1 of Week 21, 15 min before the injection of adalimumab (PK22),
Day 1 of Week 23, 15 min before the injection of adalimumab (PK23), |                                                        |

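### The protected window for the steady-state PK profile stops at 288 h, one sample before the 336 h sample that closes the profiled dosing interval

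*Protocol*

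**What the plan says.** The Synopsis (Study Therapy) gives the regimen as "80 mg SC at Week 0 followed by 40 mg SC once every two weeks, starting from Week 1". Section 1.5.1 places the intensive steady-state sampling after the 9th injection, at Weeks 15 and 16. The last sample timed in hours after that injection is PK19, at "Day 6 of Week 16, 288 h" (Table 19). The next is PK20, listed there as "Day 1 of Week 17, 15 min before the injection of adalimumab (PK20"). The Synopsis times PK20 in the same way, as 15 min ± 5 min before the 10th injection. Neither place gives hours after injection 9.

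Section 6.1.3.2, for patients in the PK study, discourages all schedule changes. It then sets two regimes:

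- A visit may, if necessary, be moved by 3 days in two periods: Visits 1 to 8 "and from Visit 11 (Week 17) to Visit 14 (Week 23").
- Deviations "starting from Visit 9 (Week 15) and to Visit 10-3 (Day 6 of Week 16) are allowed only due to AEs/SAEs".

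The abbreviations list defines Ctrough as "Measured concentration at the end of a dosing interval at steady state (taken directly before next administration") and AUCtau,ss as the area over one dosing interval at steady state. Section 4.1.2 lists both as PK endpoints, with Cav,ss, Cmax,ss and Cmin,ss. The PK analysis set (Synopsis and section 9.8) looks at attendance only up to Day 6 of Week 16.

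**The concern.** The strict window exists to protect the profile over one dosing interval, and that interval ends with the sample taken just before injection 10. The window stops at the sample before it. The visit that supplies the closing sample falls under the looser 3-day rule, and the sampling instruction does not catch a delay, because PK20 moves with the injection. The PK analysis-set rule does not catch it either: a late or missing PK20 neither excludes nor flags the patient.

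At stake is the comparability of Ctrough, and possibly of AUCtau,ss and the quantities derived from it. Samples from 72 h to 288 h carry a tolerance of 120 minutes, while the sample that closes the interval can be up to 72 hours late and still be compliant.

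**Working it through.** **1. Calendar check.** Hours after injection 9 = ((week - 15) × 7 + (day - 1)) × 24, counted from Day 1 of Week 15. This reproduces the protocol's own times:

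| Sample | Week / day | Computed | Stated |
|---|---|---|---|
| PK11 | 15 / 2 | 24 h | 24 h |
| PK16 | 15 / 7 | 144 h | 144 h |
| PK17 | 16 / 2 | 192 h | 192 h |
| PK18 | 16 / 4 | 240 h | 240 h |
| PK19 | 16 / 6 | 288 h | 288 h |
| PK20 | 17 / 1 | 336 h | none |

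The protected window ends at 288 h and the interval at 336 h.

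**2. Latest compliant PK20 without an AE.** 336 + 72 = 408 h, or 17 days. The gap from PK19 grows from 336 - 288 = 48 h to 408 - 288 = 120 h.

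**3. Effect on a trough read from PK20.** Section 1.5.1 gives a half-life t of 2 weeks on average, with a range of 10 to 20 days. Under first-order decline, C(17 d)/C(14 d) = 2^(-3/t):

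- t = 10 days: 0.812, 19% lower
- t = 14 days: 0.862, 14% lower
- t = 20 days: 0.901, 10% lower

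**4. Effect on AUC if integrated to the late sample.** With mono-exponential decline from time 0, AUC(0-17 d)/AUC(0-14 d) = (1 - 2^(-17/t)) / (1 - 2^(-14/t)):

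- t = 10 days: 0.6922 / 0.6211 = 1.115
- t = 14 days: 0.5690 / 0.5000 = 1.138
- t = 20 days: 0.4452 / 0.3844 = 1.158

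The protocol gives no absorption rate. If one of 0.2 to 0.5 per day is assumed in a one-compartment steady-state model, the trough ratio runs from 0.81 to 0.92 and the AUC ratio from 1.133 to 1.185.

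**5. Effect on AUC if cut at 336 h.** Log-linear interpolation between 288 h and 408 h returns the 336 h value exactly under mono-exponential decline. Linear interpolation at t = 10 days, scaled to 1 at time 0, uses C(12 d) = 0.4353 and C(17 d) = 0.3078. The value at 14 days is 0.4353 - (2/5) × 0.1275 = 0.3843, against a true 0.3789, so 1.4% high. At t = 20 days it is 0.4% high. AUC(0-336 h) changes by less than 0.1%.

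**6. Effect on the arm comparison.** If a fraction f of one arm slips by 3 days and the other arm does not, the Ctrough geometric mean ratio is multiplied by 2^(-3f/t). With f = 0.20 (an assumption), this gives 0.971 at 14 days, with a range of 0.959 to 0.979 for half-lives of 10 to 20 days. Equal fractions cancel and leave only extra variability.

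**The case against.** Several counter-arguments stand, and they limit the point.

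- **Postponement is not free.** A reader might infer that Visit 11 can move for any reason. Section 6.1.3.2 advises strongly against deviations and allows the 3 days only if necessary. The wording about any reasons not related to therapy applies to PK patients only from Visit 15 on.
- **Tau is still 14 days.** A reader might infer that the trial's dosing interval becomes 17 days. The nominal interval is fixed at two weeks. The 17 days are a per-patient ceiling for non-AE delays, and the documents give no frequency for such delays.
- **PK20 is not the only trough.** The Ctrough definition names no sample. PK8, taken before injection 9, also fits. Visit 9 is in the protected window, and a postponed dose shifts later visits, so PK8 keeps its 14-day spacing.
- **The AUC inflation depends on handling.** The protocol does not say that AUC will be integrated to a late sample, and interpolation to 336 h nearly removes the error. Such a rule could be in the SAP or in section 4.7.13, which is blacked out. Its absence from the visible text is not a defect.

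The window itself does not fall to these arguments. Discouragement leaves the permission in place. No analysis rule can change when the blood was drawn, and interpolation yields an estimated trough, not the measured one that the definition calls for.

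**Conclusion.** The point holds as a mismatch between the visit window and the profile it protects. Section 6.1.3.2 ends the AE/SAE-only window at 288 h and places the 336 h closing sample under a 3-day allowance, so a compliant PK20 can fall at 408 h.

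For a patient delayed the full 3 days, a PK20 trough is about 10% to 19% low. AUC is about 11% to 16% high only if it is not cut at 336 h. Both ranges assume mono-exponential decline and the protocol's half-lives of 10 to 20 days. Samples PK21 to PK23 carry the same allowance but do not close the profiled interval.

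The documents do not support a claim of bias between arms. That would need delays to differ by arm, and the study is randomised and double-blind. The consequence is some loss of precision in secondary PK endpoints. It is a minor point, worth correcting because correction is cheap.

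**What to change.** Reconcile section 6.1.3.2, the PK20 entries in Table 19 and the Synopsis, and the PK analysis-set rule in section 9.8 and the Synopsis:

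1. Let the protected PK sampling window run through the Visit 11 pre-dose sample.
2. Keep PK20 as the pre-injection sample, but add its nominal time of 336 h after injection 9 and a stated tolerance. The 120 minutes used for the neighbouring samples is the document's own reference point.
3. Compute AUCtau,ss over 0-336 h from actual sampling times.
4. Do not use a PK20 outside the tolerance as Ctrough, and say in the analysis-set rule how such a patient is handled.

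PK20 should not be separated from the Visit 11 injection. Drawing it at 336 h while the visit moves would add a visit beyond the 39 planned for PK patients and would conflict with the definition of Ctrough as a pre-dose concentration.

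The cost is amendment wording and less flexibility at one visit for at most 180 patients. Whether and when the Week 17 dose may move is for the sponsor to decide. If that flexibility is kept, items 3 and 4 still limit the effect on the PK endpoints.
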